## Abstract

**Background:** Breast cancer is the most common cancer type among women with >1million new cases worldwide. More than 40% of them will struggle with pain and fatigue years after surgery, regardless of surgical procedure. These consequences are detrimental and result in distress and disability, including work disability. Few previous attempts have been made to prevent persistent pain and fatigue after surgery by applying a psychological approach, despite psychological risk factors being crucial in the development of both persistent pain and fatigue. In this study, we aim to develop and test an easily implementable strategy of preventing persistent pain and fatigue after breast cancer surgery. The intervention strategy involves a pre-operative hypnosis session and a web-based post-operative Acceptance and Commitment Therapy. The hypnosis was previously found effective in alleviating acute post-operative pain and fatigue in breast cancer patients, while ACT may be particularly well suited to cancer populations as it offers a model of healthy adaptation to difficult circumstances. Together they form an intervention strategy with both a preventive and a rehabilitative focus.

**Methods/design:** The study will be run as a randomized controlled trial where effects of the pre- and post- operative interventions will be compared to attentional control and treatment as usual (TAU). Patients will be randomized to receive either a brief hypnosis session before surgery, and a web-based psychological intervention after surgery (ACT), or mindfulness meditation administered through a mobile app before surgery and TAU after surgery. Measurement, in the form of self-reported data and biomarker data will be assessed pre-surgery, post-surgery and 3 and 6 months after surgery.

**Discussion:** This study will be the first study to combine a pre-operative hypnosis with a post-operative ACT to prevent pain and fatigue after breast cancer surgery. The results from our study might i) help the large group of women affected by chronic pain and fatigue after breast

cancer surgery, ii) shed light on the mechanisms involved in chronic pain development, and  
iii) serve as a model for other surgical procedures.

**Trial registration:** The project will be registered in a relevant international trial register.

**Keywords:** Breast cancer; pain; post-surgical pain; fatigue; hypnosis; acceptance and  
commitment therapy

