## **Methods/Design**

### **Aims and objectives**

The primary aim of the study is to develop and test an easily implementable strategy of preventing persistent pain and fatigue after breast cancer surgery. The intervention strategy involves a pre-operative hypnosis session and a post-operative, internet-based Acceptance and Commitment Therapy (iACT). The hypnosis was previously found effective in alleviating acute post-operative pain and fatigue in breast cancer patients, while ACT may be particularly well suited to cancer populations as it offers a model of healthy adaptation to difficult circumstances. Together they form an intervention strategy with both a preventive and a rehabilitative focus.

We have the following hypotheses:

- 1) Hypnosis is more effective than one-session mindfulness in relieving acute post-surgical pain and fatigue
- 2) Hypnosis alters markers of bodily stress responses and impacts immune reactivity associated with pain and fatigue.
- 3) Hypnosis + iACT results in less post-surgical pain and fatigue and fewer medical prescriptions for pain medication 3 months after surgery compared to one-session mindfulness + TAU

- 4) Hypnosis + iACT is favorable in a cost-utility analysis, and will result in fewer days of sick leave at 1 year follow-up compared to one-session mindfulness + TAU
- 5) Hypnosis + iACT results in less psychological distress and fewer medical prescriptions for psychotropic medications at the 3 and 6-month follow-ups compared to one-session mindfulness + TAU

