## **Participants**

### ***Number and source of participants***

The study will recruit and randomize 200 participants amongst patients from the Department of Breast and Endocrine surgery at Oslo University hospital (see sample size calculations for justification).

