## **Randomization**

The randomization procedure will be administered through the program Viedoc that uses an automated and valid randomization procedure. We intend to use a stratified randomization method in order to balance the influence of covariates. The main covariates of interest here is type of surgery (mastectomy vs breast-conserving surgery) and whether the newly diagnosed breast cancer is a relapse or not. Stratified randomization is achieved by generating a separate block for each combination of covariates, and subjects are assigned to the appropriate block of covariates. After all subjects have been identified and assigned into blocks, simple randomization is performed within each block to assign subjects to one of the groups. Furthermore, a SMART randomization procedure will be applied, where the participants are randomized twice – pre-operative (hypnosis vs a one-session mindfulness), and post-operative (iACT vs treatment as usual).

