## **Analyses**

### ***Sample size and power***

Sample size is estimated for both of the primary outcomes. Previous trials with similar interventions have demonstrated moderate/large effect sizes on pain and fatigue (26, 60). However, compared to these studies, we expect more heterogeneity in our data as our study population will undergo several medical treatments during the trial (e.g. radiotherapy or chemotherapy after surgery). We thus expect a minimum difference of one point on NRS (0-10) and 3 points on FACIT-F (which corresponds to patients reporting being “slightly better”). Based on previous studies, it is expected that the control group scores 5 (SD: 2.4) on NRS at 3 months follow-up (25), and 18 on FACIT-F (26). With power set at 0.80 and two-tailed  $\alpha$  set at .05, the number needed in each group to detect the change in pain is  $n=92$ , and in fatigue  $n=87$ . To account for attrition and loss to follow-up, we plan to include 100 patients in each group.

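### The sample size assumes two groups of 100, but two randomisations of the same 200 patients leave about 50 per cell for Hypothesis 3: about 51–54% power on pain if the one-point difference is the combined-regimen effect

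*Protocol*

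**What the plan says.** The sample-size section describes one two-group comparison. It expects a minimum difference of 1 point on the NRS (control mean 5, SD 2.4) and 3 points on FACIT-F (control mean 18, no SD given). With 80% power and two-sided alpha 0.05 it arrives at 92 per group for pain and 87 for fatigue, and concludes: "To account for attrition and loss to follow-up, we plan to include 100 patients in each group". The Participants section sets the total: "The study will recruit and randomize 200 participants". The Abstract agrees with this. It names two packages, hypnosis followed by ACT, and "mindfulness meditation administered through a mobile app before surgery and TAU after surgery".

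Other sections describe a different trial. Under Randomization, "a SMART randomization procedure will be applied, where the participants are randomized twice": hypnosis or mindfulness before surgery, then iACT or TAU after it. The Design section and the Post-surgical intervention section say the same, and the Design section promises to evaluate each component both on its own and combined with the other.

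Hypothesis 3 reads "Hypnosis + iACT results in less post-surgical pain and fatigue and fewer medical prescriptions for pain medication 3 months after surgery", with mindfulness plus TAU as comparator. The Outcome Measures section assigns NRS pain and FACIT-F at 3 months to this hypothesis. The Statistical analyses section places the primary effect analysis at 3 months without naming the groups compared.

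**The concern.** Two groups of 100 exhaust the 200 patients only if there are two arms. Two successive two-way randomisations produce four sequences: hypnosis+iACT, hypnosis+TAU, mindfulness+iACT and mindfulness+TAU. Hypothesis 3 sets the first against the last, so about half of the patients lie outside its direct comparison. The sample-size text does not mention the second randomisation and does not say which two groups it means.

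At stake is whether the 80% applies to the question the trial mainly asks. If it does not, a true one-point benefit of the combined strategy would be missed about half the time, while a reader of the protocol would expect to miss it one time in five. A null result would then be over-read as evidence against the strategy. Hypotheses 4 and 5 use the same pair of regimens and would also rest on about 50 per cell.

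**Working it through.** **Inputs from the protocol.** Total 200; planned 100 per group; power 0.80; two-sided alpha 0.05; pain difference 1 point, SD 2.4; fatigue difference 3 points; stated n of 92 (pain) and 87 (fatigue).

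**Inputs that are inferred.**
- Allocation of 1:1 at each stage, giving 200/4 = 50 per cell.
- Loss to follow-up: no rate is stated. Going from 92 to 100 implies 8%, so 50 × 0.92 = 46 per cell. Going from 87 to 100 implies 13%, so 50 × 0.87 = 43.5 per cell.
- FACIT-F SD, solved from n=87 below.

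**1. Reproduce the stated figure.** Two-sample t-test, d = 1/2.4 = 0.417, 80% power, two-sided 0.05: n = 91.4, rounded up to 92. This matches, so the calculation is a plain two-group comparison with no covariate or repeated-measures gain. Power at 92 per group is 80.3%.

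**2. Pain, Hypothesis 3 with four cells.** SE = SD × √(2/n).
- n = 50: SE = 2.4 × √(2/50) = 0.480. The normal approximation gives Φ(1/0.480 − 1.96) = Φ(0.12) = 54.9%; the t-test gives 54.1%.
- n = 46: SE = 2.4 × √(2/46) = 0.500. The normal approximation gives 51.5%; the t-test gives 50.7%.
- Difference detectable at 80% power (t-test): 1.36 points at 50 per cell, 1.42 points at 46.

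**3. Fatigue.** For n = 87 and 80% power the t-test needs d = 0.427, so the implied SD is 3/0.427 = 7.02. Power for 3 points is then 56.2% at 50 per cell, 52.7% at 46 and 50.4% at 43.5.

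**4. Does using all 200 patients help?** In a balanced two-factor additive model each main effect has variance 4σ²/200 = 0.02σ². The combined effect is the sum of the two, with variance 0.04σ². This equals σ²(1/50 + 1/50). The SE is 2.4 × √0.04 = 0.48, the same as 50 against 50, so pooling under additivity gains nothing for this contrast.

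**5. What does the one point refer to?** The answer depends on this, and the protocol does not say. The even split and the additivity below are illustrations, since no component effects are given.

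| Meaning of 1 point | Hypothesis 3 power (46 / 50 per cell) | Marginal power (92 / 100 per group) |
|---|---|---|
| Effect of the package, split evenly (0.5 each) | 51% / 54% | 29% / 31% |
| Effect of each component, additive (package 2 points) | 97.7% / 98.5% | 80% / 83% |

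**6. Size needed to keep 80% for Hypothesis 3 at one point.** 92 × 4 = 368 evaluable, or 100 × 4 = 400 randomised with the protocol's own allowance.

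**The case against.** The strongest reply is that the groups of 100 are the marginal arms: all hypnosis against all mindfulness, and all iACT against all TAU. The Design section justifies double randomisation by the wish to evaluate each component, and these comparisons do keep about 100 per side. If one point is expected from each component and effects add, Hypothesis 3 has about 98% power and there is no shortfall. This stands as a possible reading, and it is why the 51–54% must be stated as conditional. But the sample-size section neither says this nor attributes the one point to a component, and no hypothesis names a marginal comparison of pain or fatigue at 3 months. Hypothesis 1 concerns acute symptoms at discharge.

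No section labels Hypothesis 3 as primary. The link is an inference, though a firm one: its outcomes and time point are those used in the sample size and in the primary effect analysis.

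Baseline adjustment could raise power, but the calculation assumes none. With 46 per cell, a correlation of 0.5 gives about 63%; about 0.7 is needed to reach 79%.

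A separate statistical analysis plan could not settle the matter alone, because the conflict is between design statements already in the protocol.

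**Conclusion.** The concern holds in conditional form. The protocol describes both a two-arm and a four-cell trial with the same 200 patients, and its sample size fits only the two-arm trial or an unstated marginal comparison. If the one-point difference is the effect of hypnosis+iACT against mindfulness+TAU, Hypothesis 3 has about 51–54% power for pain. For fatigue it is about 50–56%. These figures assume 1:1 allocation at each stage. The lower ends also use the inferred losses of 8% and 13%, and the fatigue figures the inferred SD. With no loss at all, pain power is still only 54%.

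A reader might infer two stronger things that the documents do not support. One is that Hypothesis 3 is underpowered whatever is meant; that fails if each component is expected to give a full point. The other is that making the marginal contrasts primary repairs the plan at no cost. It does not do so by itself: a one-point package effect split evenly leaves about 29–31% marginal power, and the switch changes the question. That choice belongs to the sponsor and is not a required correction.

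**What to change.** 1. Bring the Abstract, the hypotheses, the number of participants and the sample-size section into line with the Design, Randomization and Post-surgical intervention sections, so that one design is described and its allocation ratio stated.
2. In the sample-size section, name the contrast and the effect to which 92 and 87 refer, and give the FACIT-F SD and the assumed loss to follow-up.
3. If the double randomisation stays, restate power or the detectable difference for Hypothesis 3 with about 50 per cell: for pain, about 51–54% for one point, or 1.36–1.42 points at 80%.
4. If the 80% is meant for the marginal comparisons, say so and state that one point is expected from each component, with the reason for expecting it.

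The cost is protocol wording and, under the package reading, a less favourable power statement. No extra patients are needed to correct the document. Keeping 80% for one point on Hypothesis 3 would be a different decision, at about 400 randomised.

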### ***Statistical analyses***

Effect analyses of primary and secondary outcomes will be performed according to both the intention-to-treat principle and per protocol. The effect analysis of the primary outcomes will

involve a comparison of pain and fatigue levels at 3 months follow-up. Additionally, they will be analyzed using linear mixed models (also referred to as multilevel models) at the 3 different time points (post-surgery, 3- and 6-months f/u). Multilevel modelling is a flexible statistical approach that can handle non-balanced data with missing entries and repeated observations (61). The health economic analyses will investigate differences in treatment costs, as well as indirect costs related to work (dis)ability and sick-leave. A cost-utility analysis will be performed estimating costs per quality-adjusted life year.

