## **Design**

The study design involves a sequential, multiple assignment, randomized trial (SMART), where participants are randomly assigned to a treatment option at two stages, both pre- and post-surgery. By randomizing participants multiple times, we can assess the effectiveness of both interventions at each stage. We will thus be able to assess the short and long-term effectiveness of the pre-operative hypnosis, both alone and in combination with the post-operative iACT. Similarly, we will be able to assess the effectiveness of the post-operative iACT, both alone and in combination with the pre-operative hypnosis.

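### The 3-month primary comparison names no groups, and the hypothesis it seems to test (two of four cells) does not match the 100-per-group sample size (a margin)

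*Protocol*

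**What the plan says.** Protocol, Statistical analyses: the primary effect analysis will "involve a comparison of pain and fatigue levels at 3 months follow-up". No groups are named there, nor in the mixed-model sentence that follows.

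Protocol, Randomization: "participants are randomized twice", to hypnosis or one-session mindfulness before surgery and to iACT or TAU after it. This gives four cells.

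Protocol, Aims and objectives, Hypothesis 3: hypnosis + iACT is expected to give less pain and fatigue and "fewer medical prescriptions for pain medication 3 months after surgery compared to one-session mindfulness + TAU". Outcome Measures ties NRS pain and FACIT-F at 3 months to this hypothesis. The abstract describes only these two combinations, as if the trial had two arms.

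Protocol, Design: the trial is to assess the "effectiveness of the pre-operative hypnosis, both alone and in combination with the post-operative iACT", and to "assess the effectiveness of the post-operative iACT, both alone and in combination with the pre-operative hypnosis".

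Protocol, Sample size and power: "Sample size is estimated for both of the primary outcomes". The inputs are a one-point NRS difference, SD 2.4, power 0.80 and two-tailed alpha .05. They give 92 per group for pain and 87 for fatigue, with 100 per group enrolled. Number and source of participants gives 200 in total.

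**The concern.** In a two-arm trial, leaving the groups unnamed would do no harm. In a twice-randomised trial the same sentence could mean the package contrast, either margin, or an effect of one component within a level of the other. These answer different questions. If only iACT works, the iACT margin and the package contrast can both be positive while the hypnosis margin is null, and a positive package result could be misread as support for hypnosis.

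Two things are at stake. First, the contrast that the hypotheses suggest is not the one the sample size was built for, so the stated 80% power may not apply to the result the trial reports as primary. Second, with no contrast named, the choice could be made after the data are seen.

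**Working it through.** **Inputs.** Difference 1, SD 2.4, power 0.80, two-sided alpha 0.05, 100 per group, 200 in total (all from the protocol). Assumption: equal cells, because no allocation ratio is stated. Then 200/4 = 50 enrolled per cell, and 92/2 = 46 analysed per cell at the protocol's implied 8% loss. Fatigue is not recomputed because no SD for FACIT-F is given.

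**1. The protocol's own figure.** n per group = 2 × SD² × (1.960 + 0.842)² / difference² = 2 × 5.76 × 7.85 = 90.4, so 91 by the normal approximation. The two-sample t-test gives 91.4, so 92. The stated 92 is reproduced. It is a single two-group comparison at 0.05.

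**2. Which groups reach that size.** Of 200 patients in four equal cells, a margin has 100 against 100. The Hypothesis 3 contrast has 50 against 50.

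**3. Power for pain.** Standardised difference = 1 / (2.4 × √(2/n)); power from the two-sample t-test:

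| Contrast | n per group | Standardised difference | Power |
|---|---|---|---|
| Margin, as enrolled | 100 | 2.95 | 83% |
| Margin, after loss | 92 | 2.83 | 80% |
| Hypothesis 3, as enrolled | 50 | 2.08 | 54% |
| Hypothesis 3, after loss | 46 | 2.00 | 51% |

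Powering Hypothesis 3 at 80% would need 92 analysed in each of its two cells, or 4 × 92 = 368 over four equal cells, against 200 to be recruited.

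**4. What an open choice could cost.** This was simulated with no true effect, four equal independent cells and each contrast tested at two-sided 0.05. The chance of at least one false positive on one outcome is:
- package plus two margins: about 11%;
- hypnosis alone, iACT alone and the combination, each against mindfulness + TAU: about 12%;
- package plus four simple effects (each component within each level of the other): about 18%.

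These figures apply only if every contrast in the set is tested at .05 and any of them may be claimed.

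**5. A fixed sequence with the package first.** Suppose only iACT works and its effect is one point, with cells of 50. Tested alone, the iACT margin is significant about 84% of the time (normal approximation). If the package contrast must be significant first, both succeed about 53% of the time. At 46 per cell the figures are about 81% and 49–50%.

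**The case against.** The strongest reply is that the contrast can be recovered. Hypothesis 3 is the only hypothesis on pain and fatigue at 3 months, it names both sides, Outcome Measures ties the two instruments to it, and the abstract agrees. This stands in part: the candidate contrasts are not equally open. But no section calls Hypothesis 3 the primary comparison, and the sample size does not fit its two cells, so the text still supports two answers.

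A reader might infer something stronger: that the plan runs five contrasts at full alpha and lets any one of them stand as the trial's result, with 18% error per outcome, or about 31% over both outcomes at a correlation of 0.5. The protocol does not support this. The .05 appears once, in the sample-size paragraph, for one two-group comparison. The Design section says what the trial will be able to assess and attaches no test or alpha to it. Its two in-combination phrases can both mean the package contrast, which leaves three contrasts rather than five. Alpha ordering may sit in an SAP that is not shown. The two-outcome figure also brings in a separate issue.

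It can also be said that the one-point difference was meant for the package, so a margin might show less. That is fair. If two additive components each gave 0.5 points, a margin of 100 against 100 would have a standardised difference of 0.5 / (2.4 × √(2/100)) = 1.47 and power of about 31%. The protocol does not say which contrast the one point belongs to, which is a further reason to name it.

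**Conclusion.** The point holds as an internal conflict over the primary contrast. The analysis section names no groups, the hypotheses and abstract point to two of four cells, the Design section points to several effects, and the sample size fits only a margin. If Hypothesis 3 is what is meant, its power for pain is about 51–54% rather than the stated 80%. If a margin is meant, the stated power is met (80–83%), provided the one-point difference is what that single component delivers. Both statements rest on equal cells and the protocol's difference and SD.

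The false-positive chance of about 11–18% per outcome is conditional. The protocol does not say that several contrasts will each be tested at .05 and be claimable, but it does not rule it out. An SAP may settle alpha ordering. The primary contrast, and a sample size that matches it, belong in the protocol.

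**What to change.** In Statistical analyses, name one primary 3-month contrast for pain and fatigue, and bring the abstract, Aims and objectives, Design, and Sample size and power into line with it. There are two coherent choices:

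- **A margin is primary** (all iACT against all TAU, or all hypnosis against all mindfulness). The stated sample size supports this. Say that the one-point and three-point differences refer to that component, and rank Hypothesis 3 below it. The cost is that the package comparison is no longer the headline and the margin averages over the other component.
- **Hypothesis 3 stays primary.** Restate its power for pain as about 51–54% with 200 patients in equal cells. The cost is an openly underpowered primary comparison. Restoring 80% would need about 368 analysed patients, which is not a wording change.

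Under either choice, label the remaining alone and in-combination effects as secondary estimates with 95% confidence intervals and no confirmatory claim. State that a positive package contrast is not evidence for either component on its own.

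Do not place the package contrast as a gatekeeper before the margins. If only iACT works, that lowers the chance of claiming the iACT margin from about 84% to 53%.

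Apart from the choice itself, the change is to wording and needs no new data.
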